## 4.2 Medicinal Product

As the trial is non-interventional, the decision to treat subjects with REKOVELLE® will be independent from the decision to enrol the subject into the trial. Subjects will be enrolled only after the treatment decision has been made and no aspect of this trial will interfere with or influence the routine medical procedures and/or medications received. No trial medications will be provided.

REKOVELLE® (follitropin delta), solution for injection - delivered with a pre-filled injection pen, ATC code G03GA10, is a recombinant human FSH approved for the COS for the development of multiple follicles in women undergoing ART such as an in vitro fertilisation (IVF) or intracytoplasmic sperm injection (ICSI) treatments.

Subjects must be treated according to the routine clinical practice and REKOVELLE® must be prescribed in accordance with the terms of the marketing authorisation of each participating country.

According to the label the REKOVELLE® dose should be based on a recent determination of body weight and a recent determination of AMH (i.e. within the last 12 months) measured by the following diagnostic tests: ELECSYS AMH Plus immunoassay from Roche or alternatively the ACCESS AMH Advanced from Beckman Coulter or LUMIPULSE G AMH from Fujirebio.

## 4.3 Limitations of Trial Design

The trial is associated with some methodological limitations commonly found in observational studies:

- Selection Bias

Subjects will be included in the trial by approximately 15 sites known to follow-up women undergoing ART. The participating sites will be selected from private and public practice to represent all existing treatment policies and will be spread across the territory to represent as much as possible the variety of populations in the countries involved. This number of sites expected to participate in the trial may be too limited to be representative and to reflect the variety of practices in the countries involved.

Selection bias is a distortion of evidence or data that arises from the way data are collected. In order to limit bias in the selection of subjects, investigators will be asked to consecutively enrol all subjects who are prescribed REKOVELLE® for IVF/ICSI cycle, have signed informed consent and meet the selection criteria, regardless of other considerations.

To promote consecutive inclusions by investigators, this request will be regularly reminded. In addition, investigators will be asked to include all their eligible subjects to a limit of 15 during the predefined inclusion period, until the objective of 200 inclusions is reached. This procedure aims to have a representative sample of subjects treated with REKOVELLE®, based on real prescriptions, which could vary according to centres, while limiting a centre effect.

- Information Bias

Relying on investigators to fill out the assessment forms might induce the presence of missing data, which can result in bias. Entry of data via e-CRFs will minimise missing or incorrect data thanks to automated queries. Clear instructions and engagement with the trial staff, including appropriate training will minimise the amount of missing data.

- **Confounding Bias**

Confounding bias occurs when the effects of a treatment or the exposition effect of the disease vary by presence/level of another factor (effect modifier). Effect modifiers may be controlled by using stratification in the statistical analysis (subgroup analyses).

- **Lost to follow-up**

In order to assess the existence of attrition bias, the main baseline characteristics of subjects lost to follow-up will be contrasted with subjects having completed the trial. Because of the duration of the trial, the proportion of lost to follow-up subjects might not be high in proportion.

To understand the quality of life, impact, tolerability to the ART procedure with REKOVELLE® and subjects' experience of use of the REKOVELLE® Pen (ease of use, ease of training and administration) for fertility treatment, subjects will be administered a questionnaire at the clinic after cycle cancellation, trial withdrawal or before the oocyte retrieval.

Reasons for trial withdrawal will be also collected, and the characteristics of these subjects will be compared with the trial completers to detect any potential bias.

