## **STATISTICAL METHODS**

### **Statistical analysis**

This is a descriptive trial. There are no hypotheses to be tested and no inferential statistics will be applied. All descriptions of data will be based on all subjects enrolled in the trial who meet the inclusion/exclusion criteria and who receive at least one dose of REKOVELLE®. Therefore, pregnancy rates will be calculated for all subjects starting stimulation with REKOVELLE®, and mean number of oocytes, embryos, blastocysts etc. will be the mean for all subjects starting stimulation with REKOVELLE®.

Missing data for pregnancy outcomes will be regarded as “no pregnancy”. Missing data for number of oocytes, number of embryos, number of blastocysts, and similar endpoints will be regarded as zero.

The primary endpoint, real-life treatment patterns in first cycle with REKOVELLE® will be extensively described.

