| Controlled Ovarian Stimulation Period
(Refer to Table 1) | Stimulation preparation and stimulation period until oocyte retrieval.                                                                                                                                                                                                                                                                                                                       |
| Follow-up up period
(Refer to Table 1)                   | 
From oocytes retrieval through
 
 
11-week pregnancy outcomes, or
 
Negative hCG result, or
 
Negative clinical pregnancy
 
Pregnancy loss
 
Cycle cancellation or
 
 
Frozen embryo transfer cycle(s) performed within 3 months after the stimulation cycle with REKOVELLE® within the enrolment period
 |
| Trial Withdrawal                                            | Discontinuation of subject's participation in the trial irrespective of the choice, reasons for discontinuation.                                                                                                                                                                                                                                                                             |
| Treatment discontinuation                                   | Subjects who discontinue REKOVELLE® or IVF/ICSI.                                                                                                                                                                                                                                                                                                                                             |
| Lost to follow-up up                                        | Refers to Subjects who were enrolled, signed ICF and actively participating in the study but have become lost at follow-up.                                                                                                                                                                                                                                                                  |

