### 4 METHODS

#### 4.1 Trial Design

This is a European trial including Nordic Countries (Sweden, Denmark, Norway) and Switzerland. A Prospective, multi-centre, post-authorisation, non-interventional observational cohort trial conducted in routine clinical practice under real-life conditions in fertility clinics to

collect information from 200 naïve women treated with REKOVELLE® and undergoing IVF or ICSI procedures.

As the trial is non-interventional, the decision to treat subjects with REKOVELLE® will be independent from the decision to enrol the subject into the trial. Subjects will be enrolled only after the treatment decision has been made and no aspect of this trial will interfere with or influence the routine medical procedures and/or medications received. No trial medications will be provided.

In each site, during the enrolment period, consecutive women who are prescribed REKOVELLE® for IVF/ICSI cycle according to the approved label, will be invited to participate in the trial. The trial enrolment will be monitored, and the enrolment will be locked once 200 women initiated with REKOVELLE® have been enrolled. Each woman will contribute only for one stimulation cycle over the observation period.

During the observation period, the investigators will collect data for one stimulation cycle with REKOVELLE® or until early withdrawal. Data about transfer cycles using frozen embryos/blastocysts will be collected only for the first transfer cycle if they are performed within 3 months after the cycle stimulated with REKOVELLE® within the observation period.

Women with embryo/blastocyst transfer will be followed until the ongoing pregnancy (approximately 10-11 weeks after the first fresh or frozen transfer) or no pregnancy is confirmed or early pregnancy loss or trial withdrawal. Ultrasound results must be obtained if not performed at the participating site.

Baseline, COS treatment and follow-up assessments will be performed by the investigators during routine local clinical care visits.

Subject questionnaire will be completed by the subjects at the clinic after cycle cancellation, trial withdrawal or before the oocyte retrieval.

At the enrolment visit and for each eligible woman, the investigator will:

- Explain the trial to the woman, in particular, the objective of the trial and its epidemiological nature
- Give her the Informed Consent Form (ICF) and ask the subject to read and sign it to confirm her agreement to participate

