### **8.2.2 Analysis Sets**

**Analysis Population:** The Analysis Population will be defined as all subjects enrolled in the trial (signs ICF to participate in the study) who meet the inclusion/exclusion criteria and who receive at least one dose of REKOVELLE®.

**Safety Population:** The Safety Population will be defined as all subjects enrolled in the trial who received at least one dose of REKOVELLE®.

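### The baseline contrast of lost women with completers (section 4.3) cannot show attrition bias in the ongoing-pregnancy rates, because lost women stay in the denominator and count as not pregnant

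*Protocol*

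**What the plan says.** Section 4.3 (Limitations of Trial Design) introduces the check as the way to assess whether attrition bias exists: "the main baseline characteristics of subjects lost to follow-up will be contrasted with subjects having completed the trial". For withdrawals it adds that "the characteristics of these subjects will be compared with the trial completers to detect any potential bias". Neither sentence splits women by stage of treatment or by pregnancy status at last contact.

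The statistical analysis section of the protocol outline fixes how these women enter the results: "pregnancy rates will be calculated for all subjects starting stimulation with REKOVELLE" and "Missing data for pregnancy outcomes will be regarded as" no pregnancy. Section 8.2.2 defines the Analysis Population as enrolled women "who meet the inclusion/exclusion criteria and who receive at least one dose of REKOVELLE", with no requirement to complete.

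On follow-up, section 4.1 says that women with a transfer are "followed until the ongoing pregnancy (approximately 10-11 weeks after the first fresh or frozen transfer) or no pregnancy is confirmed", with pregnancy loss and withdrawal as further end points. The list of definitions also ends follow-up at a negative hCG result. Data on the first frozen transfer are collected if it takes place within 3 months of the stimulated cycle.

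**The concern.** A baseline comparison of lost women with completers suits an analysis that drops the lost women: it asks whether those who remain still resemble the whole cohort. This analysis drops nobody. A lost woman is scored as a failure, so the error she contributes depends on whether her pregnancy was in fact ongoing. Her age, AMH or weight do not show that.

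Follow-up length adds to the problem. After a given transfer, observation stops early for a negative test or a pregnancy loss and runs to about 10-11 weeks for a continuing pregnancy. Continuing pregnancies are therefore exposed to loss for longer after that transfer.

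At stake is the reading of the first two secondary endpoints, ongoing pregnancy in the fresh cycle and ongoing pregnancy including the first frozen transfer. A report could state that lost women resembled completers and conclude that attrition did not matter, while pregnancies lost from view had been counted as failures.

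**Working it through.** The protocol gives no loss rate, pregnancy rate or derived figure for this point, so there is nothing of its own to reproduce. From the documents: 200 women, all starters in the denominator, missing outcome = no pregnancy. Every rate below is an assumption.

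**1. The bias.** True rate = P(ongoing). Reported rate = P(ongoing and not lost). The difference is −P(ongoing and lost) = −p × l, where p is the true rate and l the proportion of ongoing pregnancies lost from view. No baseline variable appears.

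| True rate p | l = 5% | l = 10% | l = 20% |
|---|---|---|---|
| 20% | 19.0% (2 women) | 18.0% (4) | 16.0% (8) |
| 30% | 28.5% (3) | 27.0% (6) | 24.0% (12) |
| 40% | 38.0% (4) | 36.0% (8) | 32.0% (16) |

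Cells show the reported rate, with the number of women miscounted out of 200. The range is −1 to −8 percentage points. This shift comes from the missing-data rule. Changing the check does not remove it; the point is that the stated check does not reveal it.

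**2. What the baseline contrast shows meanwhile.** I used 4000 simulated trials of 200 women with one standardised baseline factor, about one third hCG-positive and 80% of these ongoing.

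- Loss of 10% or 20% confined to hCG-positive women, factor unrelated to pregnancy: mean standardised difference between lost women and completers 0.00, rate 2.6 or 5.3 points too low.
- Loss of 10% completely at random, factor prognostic (odds ratio 1.5 per SD): standardised difference 0.00, rate 2.7 points too low.
- Loss of 10% or 20% among hCG-positive women, factor prognostic (odds ratio 1.5 to 2.0 per SD): rate 2.7 to 5.6 points too low, and the contrast reaches p<0.05 in only 10% to 35% of trials.

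So balanced baselines are compatible with a bias of several points, even when loss is entirely random.

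**3. Precision of the contrast.** The 95% half-width of a standardised difference is 1.96 × √(1/n₁ + 1/n₂).

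- 10 lost and 190 completers: 1.96 × √(1/10 + 1/190) = 0.64 SD.
- 5 lost and 195 completers: 0.89 SD.
- Matching by stage, for example 6.25 lost and 53.75 followed among 60 ongoing pregnancies: 1.96 × √(1/6.25 + 1/53.75) = 0.83 SD, which is worse.

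**4. Who is lost if the weekly risk is equal.** Assume 20 cancelled, 100 negative, 20 early losses and 60 ongoing, followed 0, 3, 6 and 11 weeks, with a 1% weekly risk. Lost = N × (1 − exp(−0.01 × weeks)) = 0 + 2.96 + 1.16 + 6.25 = 10.4, of whom 6.25/10.37 = 60% are ongoing pregnancies. If 50 of the negatives go on to a frozen transfer and are followed 13 weeks, the share falls to about 42%. If 15 of the 60 ongoing pregnancies also come from frozen transfers followed 21 weeks, it is about 46%. The direction persists, but its strength depends on frozen transfers.

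**5. What a count by last status would show.** Take the first case in step 2 with 10% loss. Of 200 women, 66.7 are hCG-positive and 53.3 ongoing (26.7%). Of the hCG-positive women 6.7 are lost, 5.3 of them ongoing. Reported rate: (53.3 − 5.3)/200 = 24.0%. If all 6.7 are counted as ongoing: (48.0 + 6.7)/200 = 27.3%. The two figures bracket the true 26.7%.

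**The case against.** The strongest case against has four parts.

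*The protocol limits the loss.* Section 4.1 requires ultrasound results to be obtained when the scan is done elsewhere, and section 6.2.3 allows telephone follow-up. Both address the pregnant woman who moves to other care. This stands, and it bears on size.

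*Much can be derived already.* Section 8.3.4 reports positive tests, clinical pregnancy, pregnancy loss and ongoing pregnancy; section 8.2.1 reports missing counts; sections 8.3.1 and 8.3.4 report withdrawals and drop-out. The gap between these rows hints at pregnancies with unknown outcome. It is only approximate: pregnancy loss includes vanishing twin, which can coexist with an ongoing pregnancy. No listed output gives status at loss.

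*This is detail for the SAP.* Section 8.2 does leave full methods to the SAP. But section 4.3 itself names the baseline contrast as the means of assessing attrition bias, and that choice is what falls short.

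*The endpoints are secondary and descriptive.* This stands. Most of the primary endpoint is recorded before such losses occur.

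A reader might also infer more than the documents support:

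- That a baseline difference would be a false alarm reflecting only prognosis. If the lost women were mostly pregnant, the rate really is biased and the alarm is right. A difference without bias arises when the lost women are hCG-negative and of poorer prognosis (simulated standardised difference 0.63, bias 0.0), which is the opposite of what the follow-up rules favour.
- That pregnant women are always at risk longest. A woman not pregnant after a fresh transfer who has a frozen transfer within 3 months can be followed longer than one pregnant from the fresh transfer.
- That comparing baselines within the same stage would repair the check. Step 3 shows that it is too imprecise.

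**Conclusion.** The point holds in a limited form. The baseline contrast cannot serve as the test for attrition bias in the ongoing-pregnancy rates, because under the protocol's own rules that bias is set by how many lost or withdrawn women had an ongoing pregnancy. This follows from the denominator and the missing-data rule and needs no assumption about rates. Similar baselines are not evidence of no bias.

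The direction is known: the reported rates can only be too low on this account. The size is not known. The range of 1 to 8 points rests on assumed true rates of 20-40% and assumed losses of 5-20% among ongoing pregnancies, and the protocol's safeguards may well keep the loss near or below the lower end. It is a worthwhile correction to how the results are reported and does not threaten the trial's primary aim.

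**What to change.** In sections 4.3 and 8.3.1:

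1. Keep the baseline contrast as description only, and state that it is not the test for attrition bias in the pregnancy rates.
2. Tabulate women lost or withdrawn by last documented status: during stimulation; retrieval without transfer; transfer with test unknown; positive test; clinical pregnancy.
3. Beside each of the two ongoing-pregnancy rates, state how many no-pregnancy results are women last seen with a positive test or clinical pregnancy, and give the rate if all of them were ongoing. Label this an upper bound for losses after a positive test. It does not cover women lost earlier, whom the table shows separately.
4. Do not add a baseline contrast matched by stage.

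The cost is one extra table and two lines beside the rates. The transfer, pregnancy outcome and termination data are already collected under sections 6.2.3 and 6.2.4. No visit, assessment or clinical procedure changes.

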#### **4.4 Scientific Committee**

A Scientific Committee, composed by specialists in the field, will be responsible for providing advise related to trial data analysis and interpretation of results.

## **5 SELECTION OF TRIAL POPULATION**

### **5.1 Trial Population**

A total of 200 subjects who are initiated REKOVELLE® treatment for COS will be enrolled (signs ICF to participate in the study) in the trial.

This trial is intended to be conducted in a non-vulnerable population. No vulnerable subjects will be enrolled in the trial.

### **5.2 Subject Eligibility**

Subjects who meet **all** of the following inclusion criteria and who do not meet **any** of the following exclusion criteria are eligible for participation:

#### **5.2.1 Inclusion Criteria**

- Females aged 18 years or older at enrolment

- Who have never treated with (naïve) in vitro fertilisation (IVF) or intracytoplasmic sperm injection (ICSI) treatment using fresh or frozen ejaculated sperm from male partner or sperm donor
- Who are prescribed REKOVELLE® for the first time, using the dosing algorithm-based on AMH test result and body weight to define the 1st cycle dose regimen with REKOVELLE®, according to the approved label
- Who have been informed verbally and in writing about this trial content, signed the informed consent and who do not object to their data being electronically processed

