### Inclusion criteria

- Females aged 18 years or older at enrolment
- Who have never been treated with (naïve) *in vitro* fertilisation (IVF) or intracytoplasmic sperm injection (ICSI) treatment using fresh or frozen ejaculated sperm from male partner or sperm donor
- Who are prescribed REKOVELLE® for the first time, using the dosing algorithm-based on AMH test result and body weight to define the 1st cycle dose regimen with REKOVELLE® according to the approved label
- Who have been informed verbally and in writing about this trial content, signed the inform consent and who do not object to their data being electronically processed

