### 3 ENDPOINTS

#### 3.1 Primary Endpoint

Treatment patterns in first cycle with REKOVELLE®:

- Use of the algorithm-based individualised dosing regimen (daily dose of REKOVELLE® administered), number of days of treatment, dose changes ; use of the Algorithm dosing Application; use of GnRH protocol, type of GnRH protocol, triggering of follicle maturation; luteal phase support.

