### **8.3.3 Analysis of the Primary Endpoint**

The REKOVELLE® treatment patterns will be described based on the Analysis Population:

Use of the algorithm-based individualised dosing regimen (daily dose of REKOVELLE® administered, number of days of treatment); use of the Algorithm dosing Application; use of GnRH protocol, type of GnRH protocol, triggering of follicle maturation; luteal phase support. The distribution of AMH test results will be described. Characteristics of the AMH test (test type, test date) will be described.

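### Use of the dosing algorithm is about 100% by construction: eligibility requires it, and the primary endpoint is described only in eligible women

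*Protocol*

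**What the plan says.** Section 3.1 of the protocol opens the primary endpoint with "Use of the algorithm-based individualised dosing regimen (daily dose of REKOVELLE® administered), number of days of treatment, dose changes". Section 6.2.2 and Table 1 list use of the algorithm as a data item of its own, separate from use of the dosing App.

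The same feature is a condition of entry. Section 5.2.1 admits women "Who are prescribed REKOVELLE® for the first time, using the dosing algorithm-based on AMH test result and body weight to define the" first-cycle regimen according to the label, and the protocol outline carries the same criterion. Section 5.2 makes every inclusion criterion mandatory. Section 4.1 applies a related filter at invitation: "consecutive women who are prescribed REKOVELLE® for IVF/ICSI cycle according to the approved label, will be invited to participate in the trial".

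Eligibility is applied again at analysis. Section 8.3.3 states: "The REKOVELLE® treatment patterns will be described based on the Analysis Population". Section 8.2.2 defines that population as enrolled women "who meet the inclusion/exclusion criteria and who receive at least one dose of REKOVELLE".

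Section 1.2 gives the purpose as learning how the individualised regimen is used in ordinary practice. Section 4.3 says the recruitment procedure aims at a representative sample based on real prescriptions. Its discussion of selection bias covers the number and type of sites and consecutive enrolment, but not the algorithm criterion.

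**The concern.** A variable cannot be both a condition of entry and an observed outcome. If every woman described was prescribed her first-cycle regimen with the algorithm, the proportion prescribed that way carries no information about prescribing.

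The risk lies in how the result is read. A report that nearly all women were dosed with the algorithm in routine practice would look like a finding about clinics, when it only restates the inclusion criterion. The selection operates at enrolment, so an analysis plan cannot undo it for women who were never invited. The protocol describes no count of such women.

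**Working it through.** **Inputs.** Eligibility: sections 5.2 and 5.2.1. Invitation: section 4.1. Analysis set: sections 8.2.2 and 8.3.3. Planned size: 200 (section 5.1). The true rate of algorithm use, p, is not given anywhere, so I take 60% to 95% as an assumption, for illustration only. The protocol states no expected rate or precision to reproduce.

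**Step 1: the structural result.** Let A mean that the first-cycle regimen was prescribed with the algorithm, and E that all eligibility criteria are met. The criterion makes A necessary for E, so

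P(A | E, dosed) = P(A and E and dosed) / P(E and dosed) = 1.

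The true rate p drops out.

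**Step 2: at the planned size.** The result is 200/200 = 100%. An exact two-sided 95% interval would have lower limit 0.025^(1/200) = 0.982, that is 98.2% to 100%. That apparent precision comes from the selection rule, not from practice.

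**Step 3: what the design cannot distinguish.** To obtain 200 eligible women, 200/p naïve starters are needed, rounded up. The last two columns show what 200 starters not selected on the algorithm would give, with exact 95% intervals.

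| Assumed p | Starters for 200 eligible | Outside the endpoint | 200 unselected starters | 95% interval |
|---|---|---|---|---|
| 60% | 334 | 134 | 120/200 | 52.9–66.8% |
| 70% | 286 | 86 | 140/200 | 63.1–76.3% |
| 80% | 250 | 50 | 160/200 | 73.8–85.3% |
| 90% | 223 | 23 | 180/200 | 85.0–93.8% |
| 95% | 211 | 11 | 190/200 | 91.0–97.6% |

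As written, every row reports 200/200.

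**Step 4: which components are affected.** The criterion concerns how the first regimen was prescribed. Section 8.3.3 lists "Use of the algorithm-based individualised dosing regimen (daily dose of REKOVELLE® administered, number of days of treatment); use of the Algorithm dosing Application". The administered dose, the number of days and App use are not fixed by the criterion. Nor are dose changes, the GnRH protocol and its type, the trigger, or luteal support.

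**Step 5: where women not prescribed with the algorithm appear.** Those never invited appear nowhere. Those enrolled in error appear in the disposition summary (section 8.3.1) and the Safety Population (section 8.2.2), but not in the primary description.

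**Step 6: dose changes.** This component is in the primary endpoint (section 3.1 and the outline) and in Table 1. It is missing from the treatment data list in section 6.2.2 and from the primary analysis in section 8.3.3.

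**The case against.** The best defence is that the protocol openly describes an on-label cohort. Sections 4.1 and 4.2 say treatment follows the marketing authorisation, and the primary objective is usage patterns, not the share of prescribers who use the algorithm. The trial is descriptive with no hypothesis, and full analysis detail is left to the statistical analysis plan. This stands as a reason to keep the criterion. It is not a reason to list algorithm use as something observed.

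It is also fair that 100% is not a strict certainty. No section says the dose is recomputed to judge eligibility, and section 10.2 provides source verification for only a defined percentage of subjects. A woman recorded as prescribed with the algorithm, whose dose does not match it, could remain in the Analysis Population and be seen. Hence about 100%.

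A reader might infer four stronger things that the protocol does not support:

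- **That the primary endpoint as a whole is empty.** Most components can vary (step 4).
- **That dose changes are the only component able to show departures.** The administered daily dose and days of treatment are both collected and analysed. The dose-changes omission is a separate wording mismatch, not evidence of selection.
- **That the overstatement is, say, 10 to 30 percentage points.** Any such size is an assumed rate restated as bias.
- **That describing the endpoint on the Safety Population would cure the problem.** Its members were enrolled under the same criterion, so it recovers only women enrolled in error.

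**Conclusion.** The point holds for one component: use of the algorithm to set the prescribed first-cycle regimen. It is fixed at or near 100% by eligibility and by the analysis set, and it says nothing about how often clinics use the algorithm. This follows from the protocol's text and needs only that the eligibility criteria are applied as written. Section 4.3 should acknowledge it.

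The size of any overstatement is unknown; the table in the working is illustrative. Because the other components remain informative and the remedy is mainly wording, this should be fixed, but it does not invalidate the trial. I take no view on which dose is right.

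**What to change.** 1. Do not report algorithm use as an observed rate. Restate the primary objective and endpoint as patterns of use among women prescribed with the algorithm, in the outline and in sections 2.1, 3.1 and 8.3.3, and name this selection in section 4.3.
2. In section 8.3.3, replace the yes/no description of algorithm use with concordance: recompute the algorithm dose from recorded AMH and weight, compare it with the daily dose administered, and give the proportions equal, lower and higher. Keep women whose recorded dose does not match in this description, and show the Safety Population as a sensitivity display. AMH and weight are collected under section 6.2.1 and the administered dose under section 6.2.2.
3. Add dose changes to sections 6.2.2 and 8.3.3, to agree with section 3.1 and Table 1.
4. Optionally, have each site supply an anonymous count of first REKOVELLE® prescriptions not enrolled because the algorithm was not used. Only this step gives information on women outside the cohort.

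The cost is protocol wording, a narrower stated objective and one derived variable from data already planned. The optional count adds a small burden at up to 15 sites.
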